## Abstract

**Introduction:**

Physical rehabilitation delivered early following admission to the intensive care unit (ICU) has the potential to improve short-term and long-term outcomes. The use of supine cycling together with other rehabilitation techniques has potential as a method of introducing rehabilitation earlier in the patient journey. The aim of the study is to determine the feasibility of delivering the designed protocol of a randomised clinical trial comparing a protocolised early rehabilitation programme including cycling with usual care. This feasibility study will inform a larger multicentre study.

**Methods and analysis:**

90 acute care medical patients from two mixed medical–surgical ICUs will be recruited. We will include ventilated patients within 72 hours of initiation of mechanical ventilation and expected to be ventilated a further 48 hours or more. Patients will receive usual care or usual care plus two 30 min rehabilitation sessions 5 days/week.

Feasibility outcomes are (1) recruitment of one to two patients per month per site; (2) protocol fidelity with >75% of patients commencing interventions within 72 hours of mechanical ventilation, with >70% interventions delivered; and (3) blinded outcome measures recorded at three time points in >80% of patients. Secondary outcomes are (1) strength and function, the Physical Function ICU Test–scored measured on ICU discharge; (2) hospital length of stay; and (3) mental health and physical ability at 3 months using the WHO Disability Assessment Schedule 2. An economic analysis using hospital health services data reported with an embedded health economic study will collect and assess economic and quality of life data including the Hospital Anxiety and Depression Scales core, the Euroqol-5 Dimension-5 Level and the Impact of Event Score.

**Ethics and dissemination:**

The study has ethical approval from the South Central Hampshire A Research Ethics Committee (19/SC/0016). All amendments will be approved by this committee. An independent trial monitoring committee is overseeing the study. Results will be made available to critical care survivors, their caregivers, the critical care societies and other researchers.

**Trial registration number:**

NCT03771014.

Strengths and limitations of this studyWill investigate the implementation of a protocolised early rehabilitation intervention that is usual care in one NHS/university teaching institution, into other NHS institutions with different organisational structures.The defined cohort has been demonstrated to benefit from this type of rehabilitation in alternative healthcare systems.Results will inform the design of a multicentre randomised controlled trial.This study is not designed to assess the effectiveness of the intervention.Inability to blind the intervention to patients, physiotherapist and clinicians involved in the delivery of the intervention.

## Introduction

In 2018/2019, there were over 290 000 admissions to adult intensive care units (ICUs) in the UK.^1^ Treatment advances have reduced mortality associated with critical illness^2 3^; however, survival does not represent the end of the story.^4^ A complex interplay between baseline health status, acute disease and the traumatic effects of intensive care treatment is associated with long-term physical, psychological and social hardship.^5–10^ Patients discharged from the ICU have higher mortality, higher health service costs and a reduction in employment status compared with hospitalised patients not requiring ICU.^8 11^

ICU-acquired weakness is characterised by rapid muscle wasting, polyneuropathy and bone demineralisation, causing pain, weakness and impaired physical function.^12–14^ Contributing factors are multifactorial, although immobility due to the sedation required for tolerance of ventilation plays an important role.^15 16^ Early mobilisation may mitigate these effects.^17–19^ In 2009, Schweickert *et al* reported that patients who underwent early physical therapy (within 1.5 days of mechanical ventilation) had greater functional independence at hospital discharge than patients who had usual care physical therapy.^20^ A recent randomised controlled trial (RCT) on the impact of a progressive ICU mobility programme reported improved functional status at ICU discharge.^21^ Meta-analyses and systematic reviews report that early mobilisation of ICU patients may reduce duration of mechanical ventilation and improve short-term physical outcomes,^22–24^ but mobilisation can be difficult to implement during a patient’s stay in the ICU. Moreover, studies which used delayed rehabilitation, often more than a week after ICU admission,^25–27^ have not replicated these outcomes.^28–34^ Barriers to early mobilisation include heavy sedation, patient’s illness, lack of resources and/or clinician buy-in.^35–38^In-bed cycle ergometry can provide passive activity in heavily sedated patients who are receiving vasopressors^39 40^ with minimal physiological demand^40 41^ and can be transitioned to active cycling as the patient’s condition improves.^23 42–44^

We implemented cycle ergometry as part of an early protocolised rehabilitation quality improvement programme with physiotherapy technicians supporting the additional workload.^45^ Like other investigators, we reported reduced number of ventilator days and ICU length of stay.^21 46–49^

The primary aim of this study was to evaluate the feasibility of an RCT investigating the effect of early protocolised rehabilitation versus usual physiotherapy care in ICU patients. Results will inform a prospective fully powered multicentre RCT. This protocol is reported according to Standard protocol items for clinical trials (SPIRIT 2013 Statement)^50^ and Template for Intervention Description and Replication^51^ guidelines.

### Aim

The aim of this study was to determine the feasibility of delivering study procedures comparing an early protocolised mobilisation programme that includes cycling with usual care.

### Objectives

Feasibility will be determined by measures of the recruitment process, intervention fidelity and outcome measurement completeness, specifically, (1) study accrual rates: a minimum of 30% of eligible patients or one to two patients per site per month are enrolled; (2) protocol adherence: 75% of patients commencing intervention within 72 hours of ICU admission, with a minimum of 70% of planned interventions delivered; and (3) blinded outcome assessment: functional assessment performed at three time points in 80% of survivors. The results will inform a larger fully powered RCT.

## Methods and analysis

### Study design

This is a two-centre feasibility study using a two-arm RCT, randomised 1:1, with blinded outcome assessments at ICU discharge, hospital discharge and 3-month follow-up. Patients will be recruited from two general ICUs, located in the south of the UK. They will not be recruited from our ICU on account that the intervention is now standard practice at this site. Prior to each site opening to recruitment, an audit of current physiotherapy practice will be undertaken over a 4-week period to evaluate what constitutes ‘usual care’ in each institution.

### Participants

Ninety patients will be recruited. Eligible patients will be over 42 years old and will have an acute/unplanned medical admission to the ICU. They will be functionally independent prior to ICU admission (Barthel Index>80), in the hospital for <5 days prior to intubation and ventilation, intubated and ventilated for <72 hours, and expected to remain ventilated for a further 48 hours. Patients will be excluded if they are in the hospital for 5 days or more prior to ICU admission, have acute brain or spinal cord injury, known or suspected neurological/muscular impairment, condition limiting use of cycle ergometry (eg, lower limb fracture/amputation), not expected to survive >48 hours decided by consulting an intensivist and persistent therapy exemptions in the first 3 days of mechanical ventilation. Figure 1 presents the planned flow of patients through the study.

**Figure 1 F1:**
[figure not shown]
Study design. CFS, Clinical Frailty Score; CPAx, Chelsea Critical Care Physical Assessment Tool; EQ-5D-5L, Euroqol-5 Dimension-5 Level; HAD, ICU, intensive care unit; IES, Impact of Event Score; WHODAS 2.0, WHO Disability Assessment Schedule 2.

### Recruitment, consent and randomisation

The study team will screen all patients for eligibility. Recruitment began in June 2019 (and was temporarily suspended in March 2020 due to the COVID-19 pandemic). It is anticipated recruitment will continue until mid 2022. The majority of patients will have diminished capacity when first eligible; therefore, the consent process is multilayered and designed in accordance with the Mental Capacity Act (MCA) 2005^52^ (figure 2):

*Patient informed consent*: wherever possible, informed consent will be directly sought from the patient (see online supplemental files 1 and 2).*Personal consultee informed assent*: if the patient is unable to provide consent, informed assent will be sought from the patient’s personal consultee, within 6 hours of confirmation of eligibility. If the personal consultee is not available in person, attempts will be made to contact them by telephone. They will be asked to provide written assent, at the earliest possible convenience (see online supplemental files 3 and 4).*Professional consultee informed assent:* where both patient and personal consultee are not available to approve enrolment within 6 hours of confirmation of eligibility, assent will be sought from a professional consultee in accordance with the MCA. The professional consultee will be a consultant medical practitioner, independent from the study. The patient’s personal consultee will be consulted at the earliest possible opportunity and assent will be requested to continue in the study.

**Figure 2 F2:**
[figure not shown]
Consent pathway.

In all cases, once the patient has regained capacity, they will be informed of the study and consent continuation will be sought. Following consent or assent, patients will be registered on a bespoke electronic data collection tool (ALEA) and randomly assigned to the protocolised early rehabilitation or usual care.

### Staff training/site set-up

Participating sites will employ the equivalent of a full-time therapy technician to deliver the study intervention, under the supervision of a senior critical care therapist. Both senior critical care therapists and therapy technicians will complete a training package delivered by the primary institution (University Hospital Southampton NHS Foundation Trust), where early rehabilitation with cycling is well established and embedded in usual care. This package includes seminars on the delivery of the protocolised early rehabilitation, use of the bespoke electronic database and 5 days of clinical shadowing.

### Interventions

All patients will receive usual medical, nursing and physiotherapy care while in intensive care. Each bedside nurse will be asked at the start of the shift if they have been involved caring for a patient in the intervention arm of the study. The ICU physiotherapy team, who are not involved with the delivery of the study delivery, will deliver all usual physiotherapy interventions in both groups. The physiotherapist delivering usual care will be asked to verify if they have delivered any of the study interventions. In the intervention arm, the protocolised physiotherapy programme will commence within 72 hours of ICU admission or as soon as possible thereafter and will continue for 28 days or until ICU discharge, whichever occurs first. Patients’ respiratory support can range from full mandatory ventilation through to oxygen supplementation with no mechanical support following extubation. Sedation is targeted throughout the time that the patient is intubated, and the ventilation mode is adjusted to patients’ needs, compliance and comfort at discretion at the start of each physiotherapy intervention, the participants’ level of sedation will be assessed using the Richmond Agitation–Sedation Scale (RASS)^53 54^ and the Confusion Assessment Method for ICU^55^will be undertaken. RASS will be targeted to a RASS between −1 and +1 by the bedside nurse. After 28 days of ICU admission, all patients will receive usual care physiotherapy interventions.

### Group 1: usual care control group

In this pragmatic study, physiotherapy interventions will be guided by individual assessment and start in accordance with the usual care pathway within each institution. The focus of each session may be respiratory support, mobilisation or a combination of both. Interventions delivered will be determined by the physiotherapist in conjunction with the attending physician. Interventions include, where appropriate, passive or active range of movement, positioning and respiratory physiotherapy, and when able, sitting on the edge of the bed, standing (assisted or unassisted), standing to transfer to chair, marching on the spot and walking (figure 3). Usual interventions may occur at any time of day.

**Figure 3 F3:**
[figure not shown]
Study intervention pathway. (PROM = Passive Range of Movement)

### Group 2: Protocolised rehabilitation pathway

Patients will have usual care physiotherapy, in addition to the two protocolised intervention within 72 hours of ICU admission or as soon as possible thereafter. Patients will be screened for safety criteria to withhold the intervention prior to each planned intervention session (table 1).

**Table 1 T1:** Safety criteria for delivery of physical therapy interventions

	Criteria to commence physiotherapy	Criteria to stop/withhold physiotherapy intervention
Blood pressure	Mean Arterial Blood Pressure (MAP) 60–100 mm Hg, no change in vasopressor dose requirement for preceding 2 hours	Catecholamine-resistant hypotension with MAP <60 mm Hg
Heart rate	Between 40 and 140 beats/min	<50 or >140 beats/min
Respiratory rate	Sustained <40 breaths/min	Sustained >40 breaths/min
Temperature		>40°C
Oxygen requirement	If Fraction inspired oxygen (FiO_2_)>0.8 for passive exercise only	
	FiO_2_ <0.8 and (Positive End Expiratory Pressure) PEEP <15 cmH_2_O	
Desaturation		Sats fall <85% for>1 min
Other		Fall. Unplanned extubation. Acute bleeding. New-onset arrhythmia. Signs/symptoms of acute myocardial ischaemia. Patient pain/distress. Clinical team decides therapy intervention not appropriate. Refusal by patient or representative.

Those meeting criteria to withhold interventions will have issues addressed and reassessed for interventions 2 hours later. The two additional rehabilitation sessions will be delivered by the research physiotherapy staff including a therapy technician. This will comprise two mobility sessions the modality of the first, chosen at the discretion of the physiotherapist. The second session will be 30 min of supine cycling delivered in the afternoon.

The first rehabilitation intervention each day will be delivered in the morning. Planned interventions include passive or active range of movements, passive cycling, active cycling, in-bed exercises, sitting, mobilisation out of bed and walking. Daily assessment of the patient will be made to ensure the highest level of activity possible is provided for each individual patient given safety considerations and capability of the patient.

The second session will be cycling based. An in-bed supine cycle ergometer (MotoMed Letto 2) will be used to engage the participant in passive, assisted or active cycling, or a combination, depending on the degree of patient cooperation (figure 3). The aim was for the patient to have 30 min of cycling per day, following a standardised cycling programme. If cycling is in passive mode, patients will commence cycling at 5 revolutions per minute (RPM), building up to 20 RPM over 5 min and continue this for 20 min before 5 min 5 RPM cool down. In the assisted or active mode, after the 5 min warm-up, cycling will continue for 20 min at patient-selected RPM followed by a 5 min cool-down at 5 RPM. In-bed cycling sessions will stop when the patient is deemed to be able to stand and transfer from bed to chair for both mobility sessions for two consecutive days. If patients are considered unable to have concurrent mobility therapy and respiratory weaning, mobility therapy will take priority, in agreement with the senior clinical team. Individual participants will receive the trial intervention on 5 days/week (Monday–Friday) for the duration of their ICU stay or a maximum of 28 days, whichever comes first. Patients will be monitored for cardiovascular and respiratory stability and safety of indwelling lines, tubes and catheters with predetermined criteria for termination of any session (table 1). Deviations from the planned protocol will be reported to determine potential barriers to implementation. Patients will be able to decline any intervention or outcome assessment at any time without compromise to their care.

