### Safety and adverse events

Early mobility within ICUs is safe. In a review of physiotherapy in a critical care rehabilitation programme, 1110 patients underwent 5267 rehabilitation sessions; physiological abnormalities or potential adverse events occurred in only 6 per 1000 interventions.^77^ Mobilisation interventions will only be delivered if patients fit the safety criteria defined in table 1. Similar safety criteria have been used in other ICU rehabilitation studies.^78 79^

All adverse events will be documented. Any intervention will cease according to stopping criteria detailed in table 1. Any such event will be recorded as an adverse event. The chief investigator will provide a monthly update to the safety monitoring committee. Serious adverse events are events that result in death, are life-threatening or require prolonged hospitalisation. Any such event will be reported in accordance with the NHS Health Research Authority guidance.

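### Table 1 lets a session start at a heart rate of 40 to 49 beats/min, a range in which the same table says to withhold or stop it

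*Protocol article*

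**What the plan says.** Table 1 of the protocol article has one column of criteria to commence physiotherapy and one of criteria to stop or withhold it. The heart-rate row reads:

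- Commence: "Between 40 and 140 beats/min"
- Stop or withhold: "<50 or >140 beats/min"

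The text around the table sets out how it is used:

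- Before a session: "Patients will be screened for safety criteria to withhold the intervention prior to each planned intervention session (table 1").
- If a withhold criterion is met: "Those meeting criteria to withhold interventions will have issues addressed and reassessed for interventions 2 hours later".
- During a session, patients are monitored against "predetermined criteria for termination of any session", again with reference to Table 1.

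The section Safety and adverse events adds a condition for delivery, "Mobilisation interventions will only be delivered if patients fit the safety criteria defined in table 1", and a rule for cessation, "Any intervention will cease according to stopping criteria detailed in table 1. Any such event will be recorded as an adverse event".

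**The concern.** The two cells give opposite instructions for the same patient at the same moment. Someone with a heart rate in the forties is fit to commence under one column and must be withheld under the other.

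This is a bedside safety limit for critically ill patients, used before and during sessions at two sites. Staff who apply the withhold screen will not treat at 40 to 49 beats/min. Staff who look only at the commence column could begin a session that already meets a stopping criterion. That session would have to end at once and would be recorded as an adverse event. The study is also meant to inform a larger multicentre trial, so an uncorrected cell could be carried into it.

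**Working it through.** No figure in the plan depends on this point, so there is none to reproduce. The check compares the two columns of Table 1 and then asks whether the text resolves the difference.

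**1. Overlap in the heart-rate row.**

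- Commence set: 40 to 140.
- Stop/withhold set: below 50, or above 140.
- Intersection at the lower end: 40 ≤ rate < 50, with 40 itself included only if the stated range includes its ends. Width: 50 − 40 = 10 beats/min.
- Intersection at the upper end: none, because 140 is the limit in both cells.

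**2. The other limits that carry a number in both columns.**

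| Limit | Commence | Stop/withhold | Difference |
|---|---|---|---|
| Mean arterial pressure, lower (mm Hg) | 60 | 60 | 0 |
| Heart rate, lower (beats/min) | 40 | 50 | 10 |
| Heart rate, upper (beats/min) | 140 | 140 | 0 |
| Respiratory rate, upper (breaths/min) | 40 | 40 | 0 |

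Three of the four numbers agree. The lower heart-rate limit is the only one at which a patient can satisfy both columns.

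**3. Could these be a start limit and a separate in-session stop limit?** No, for two reasons. First, the second column covers withholding as well as stopping, and the text screens on the withhold criteria before each planned session, so the limit of 50 applies at the same time as the limit of 40. Second, the direction is wrong: a start limit looser than the stop limit admits patients to sessions that must end immediately.

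**4. Does the text say which column governs?** Not expressly. It does point one way. Reassessment after 2 hours is directed for anyone meeting a withhold criterion, with no exception for those who also meet a commence criterion. Delivery is conditional on fitting the criteria in the table, and a stopping criterion ends the session. With both cells taken as printed, a patient at 45 beats/min is withheld, and the commence cell is too loose.

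**5. Effect of a correction.** With a commence range of 50 to 140, the overlap with below 50 or above 140 is empty. Changing the stop/withhold limit to below 40 would also empty it.

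**The case against.** Four arguments can be made on the other side.

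- **The direction is not proved.** Outside its own cell, the number 50 appears nowhere as a heart-rate limit. The sentences on screening, reassessment and cessation would read equally well with a limit of 40 there, so the slip could be in the stop/withhold cell. This stands. The text shows which column prevails as printed, not which number was meant.
- **Practice is largely protected.** Read cumulatively, the two columns lead to withholding. Table 1 also lets the clinical team judge therapy inappropriate, and the technician is employed to "deliver the study intervention, under the supervision of a senior critical care therapist". This also stands: a wrong start requires someone to overlook the screening sentence. It limits the harm but does not make the table consistent.
- **The columns are not mirror images elsewhere.** The stop cell for blood pressure adds a qualifier of catecholamine resistance. A pressure of 55 mm Hg without it, or one above 100, falls in neither column, as does a respiratory rate of exactly 40. This is correct, so the comparison above is of printed numbers only. Those cases are gaps between the columns, however, and not a patient told both to start and not to start. The heart-rate overlap needs no support from the comparison.
- **The article condenses a fuller protocol.** The sites may work from a correct table. That cannot be seen here. The point concerns two legible numbers that disagree, not an omission that a fuller document would fill.

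**Conclusion.** The inconsistency is real and plain in the current text: for heart rates from 40 up to but not including 50 beats/min, Table 1 both permits and forbids a session. Confidence in the mismatch is high. That 40 is the wrong number is conditional on giving effect to both cells as printed and to the sentences that apply them.

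The severity is minor. How often a patient is screened in this range cannot be determined from the document and is probably small. No sample size, confidence interval or analysis depends on it, and no effect on the 70% delivery measure is claimed.

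**What to change.** The investigator and safety committee should confirm the intended lower heart-rate limit and use it in both columns of Table 1. Unless they have a clinical reason for 40, the default should be 50: it is the more cautious value and the one that governs when both cells are applied as printed. The commence cell would then give a range of 50 to 140 beats/min. They should also check whether the sites' working documents carry the same discrepancy and correct them if so.

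The cost is one table cell and that check. If a site has been starting sessions at 40 to 49 beats/min, a few more sessions may be withheld and reassessed after 2 hours.
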